## Trial status

The first patient was enrolled in August 2014. Initially the IMPRESSION study was planned to include STEMI patients only. However, on 9 September 2014, after the approval of the Local Ethics Committee, the trial population was expanded to include subjects with NSTEMI as well. By 8 January 2015, 33% of planned patients were successfully included in the study. The baseline characteristics of the enrolled patients are presented in Table 2.

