**Methods/design:**

The IMPRESSION study is a phase IV, single center, randomized, double-blind, placebo-controlled clinical trial that is designed to assess the influence of morphine on the pharmacokinetics and pharmacodynamics of ticagrelor in patients with myocardial infarction. The study is planned to include up to 100 patients with myocardial infarction who will be randomized into one of two arms in a 1:1 ratio. Subjects in the intervention arm prior to the loading dose of ticagrelor (180 mg) will receive morphine (5 mg) intravenously, whereas patients in the control arm will receive a placebo prior to the loading dose of ticagrelor (180 mg). The pharmacokinetics of ticagrelor and its active metabolite (AR-C124910XX) will be assessed by liquid chromatography mass spectrometry. Platelet function testing in each patient will be performed using up to four different methods (platelet vasodilator-stimulated phosphoprotein assay, multiple electrode aggregometry, VerifyNow, and light transmission aggregometry).

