### Statistics

Since there is no reference study examining the PK of ticagrelor in patients presenting with STEMI or NSTEMI, we decided to perform an internal pilot study of approximately 30 patients (15 patients for each arm) to estimate the final sample size. The means and standard deviations of AUC_(0–12)_ for ticagrelor in the first 33 patients assessed for patients who received morphine and for patients who received the placebo were 6,917 ± 4,920 and 10,379 ± 5,996 ng · h/ml, respectively. Based on these results and assuming a two-sided alpha value of 0.05, we calculated, using the *t*-test for independent variables, that enrollment of 68 patients would provide an 80% power to demonstrate a significant difference in AUC_(0–12)_ for ticagrelor between patients who received morphine prior to a loading dose of ticagrelor and those who received the placebo prior to the ticagrelor loading dose.

Continuous variables will be compared between both study arms by the Student’s *t*-test or the Mann–Whitney *U* test, depending on the presence or absence of the normal distribution (as assessed by the Kolmogorov-Smirnov test). Proportions will be compared by the Fisher exact test or chi-square test when appropriate. Pharmacokinetic calculations will be performed using a dedicated software.

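### The article gives two incompatible planned sizes, 68 and 100, and the stated 80% power matches neither (about 73% at 68, about 88% at 100)

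*Protocol article*

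**What the plan says.** Three places in the protocol article bear on the planned size.

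- **Abstract, Methods/design:** "The study is planned to include up to 100 patients with myocardial infarction", "randomized into one of two arms in a 1:1 ratio".
- **Statistics:** the team ran an "internal pilot study of approximately 30 patients (15 patients for each arm) to estimate the final sample size". The AUC(0–12) means and SDs in the first 33 patients, morphine then placebo, "were 6,917 ± 4,920 and 10,379 ± 5,996 ng · h/ml, respectively". From these, "assuming a two-sided alpha value of 0.05", the authors report that "enrollment of 68 patients would provide an 80% power".
- **Trial status:** by 8 January 2015, "33% of planned patients were successfully included in the study". Table 2 in the same section shows 33 patients.

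The article does not say how 68 and 100 relate. It gives no allowance for dropout or non-evaluable samples that would link them.

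**The concern.** The pilot was run to fix the final size, and the Statistics section reports its answer as 68. The Trial status section then measures progress against 100, although the same 33 patients had already been used to obtain 68. A reader cannot tell at which number enrolment ends, and so cannot tell what power the trial has.

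The ambiguity matters more than usual here because the primary endpoint has already been summarised by arm. A final size fixed without regard to the data leaves the 5% level intact. A choice between 68 and 100 made with knowledge of the results might not, and the printed text does not rule that out.

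**Working it through.** **1. Which planned size does 33% imply?**
Inputs: 33 enrolled (Table 2); 68 (Statistics); 100 (abstract).
33/100 = 33.0%, while 33/68 = 48.5%. The Trial status figure therefore uses 100.

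**2. Is 68 reproduced from its own inputs?**
Inputs (Statistics): means 6,917 and 10,379; SDs 4,920 and 5,996; two-sided 0.05; 80% power; independent-samples t-test. Allocation is 1:1 (abstract).

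- Difference: 10,379 − 6,917 = 3,462.
- Common SD for equal arms: √[(4,920² + 5,996²)/2] = √30,079,208 = 5,484.5.
- Standardised difference: d = 3,462/5,484.5 = 0.631.
- Normal approximation: n per arm = 2(1.960 + 0.842)²/d² ≈ 15.70/0.3985 ≈ 39.4, so 40 per arm and 80 in total.
- Exact t-test (noncentral t): 41 per arm, 82 in total.

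So 68 is not reproduced. Pooling with 16/17 or 17/16 patients per arm, or averaging the two SDs, also gives 80 to 82. One-sided versions using both SDs give 62 to 64. The placebo SD alone gives 96 to 98 (two-sided). The morphine SD alone with a two-sided t-test gives 66, the nearest result, but the article does not state that basis.

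**3. Power at each stated size**
Two-sided t-test at 0.05, d = 0.631, noncentrality d√(n/2) with n per arm:

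| Total | Per arm | Noncentrality | Power |
|---|---|---|---|
| 68 | 34 | 0.631 × √17 ≈ 2.60 | 72.7% |
| 100 | 50 | 0.631 × √25 ≈ 3.16 | 87.8% |

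**4. Type I error**
Simulated trials with no effect, normal data and unadjusted two-sided t-tests at 0.05 (200,000 trials; a separate run of 400,000 in parentheses):

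| Scenario | Type I error |
|---|---|
| Size fixed at 68 | 5.1% (5.0%) |
| Size fixed at 100 | 5.0% (4.9%) |
| 68 or 100, chosen without regard to the data | (4.9%) |
| Test at 68; if not significant, test at 100 | 7.7% (7.6%) |
| Tests at 33, 68 and 100 | 10.8% (10.7%) |
| Size set from the observed effect and SD at 33, capped at 100, one final test on all patients | (6.6%) |

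The last three rows are assumed scenarios. The article announces no test at 33, and no test at 68 followed by continuation.

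**5. What was known at 33 patients**
Assuming a 16/17 split, which the article does not state, the printed summaries give t ≈ 1.81 and p ≈ 0.08.

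**The case against.** The best defence is that 100 is a ceiling and 68 is the powered number beneath it. The abstract does say up to 100, and the Statistics section says what 68 would provide, not that recruitment stops there. A ceiling set first, a pilot-based 68 later, and progress counted against the ceiling would be a coherent history. The gap could also be an allowance for non-evaluable patients. This is possible, but the article does not say so. The Trial status section treats 100 as the planned number, and the pilot's declared purpose was the final size. Nor does this reading rescue the power statement, since 68 falls short of 80% on the printed inputs.

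A second defence is that closing rules and interim testing are commonly left to the full protocol or SAP, which are not shown. That stands: a stopping rule cannot be presumed absent from the plan. It does not cover printed numbers that disagree with each other.

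A reader might infer from the two sizes that the 5% level is already lost. The documents do not support that. At either fixed size the error is about 5%, and the Statistics section uses the 33-patient data for sizing only, without reporting a test or an option to stop. With p of about 0.08 under the assumed split, significance at 5% was not available at that look in any case.

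**Conclusion.** The point holds as an inconsistency in planned size, with a power figure that is wrong for either number. It rests on the printed pilot means and SDs, equal arms and a two-sided t-test at 0.05. On that basis 68 has about 7 percentage points less power than stated, and 100 about 8 points more.

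The type I error part is conditional. What the text supports is narrower than inflation: results by arm were known at 33 patients, the 68 was derived from the observed difference, and the printed text leaves the end of enrolment open. The 6.6%, 7.7% and 10.8% figures show what certain unadjusted uses of that freedom would cost; they do not describe what the article plans.

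**What to change.** Put one final size, with its correct power, in the abstract, Statistics and Trial status:

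- **100:** state about 88% power. The 33% can stay. This adds no patients beyond the stated maximum, but up to 32 more than 68 (100 − 68).
- **68:** state about 73% power, replace up to 100 with 68, and change 33% to 49% (33/68 = 48.5%).

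In either case, explain in one sentence how 68 and 100 relate, and state that the primary endpoint is not tested before the final size is complete.

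Also acknowledge that fixing the number now does not remove the effect of having sized the trial from the arm difference seen at 33 patients. Keeping 100 avoids that data-driven choice, provided 100 was set before those results were known; the article should say whether it was. If 68 is kept, the final analysis should account for how it was chosen. Apart from the extra patients if 100 is chosen, the cost is wording.

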**Table 2 Tab2:** **Baseline characteristics**

	**STEMI (n = 22)**	**NSTEMI (n = 11)**	**Total (n = 33)**
Age in years, median	62.6	62.4	62.5
Age ≥ 70	9 (40.9%)	2 (18.2%)	9 (27.3%)
Female	5 (22.7%)	2 (18.2%)	7 (21.2%)
Hypertension	7 (31.8%)	8 (72.7%)	15 (45.5%)
Diabetes mellitus	5 (22.7%)	2 (18.2%)	7 (21.2%)
Dyslipidemia	19 (86.4%)	8 (72.7%)	27 (81.8%)
Current smoker	9 (40.9%)	6 (54.5%)	15 (45.5%)
Prior MI	1 (4.5%)	3 (27.3%)	4 (12.2%)
Prior PCI	1 (4.5%)	5 (45.5%)	6 (18.2%)
Prior CABG	0	0	0
BMI in kg/m^2^	28.4	27.4	28.1

BMI: body mass index; CABG: coronary artery bypass surgery; MI: myocardial infarction.

## Abbreviations

ACCF/AHA: American College of Cardiology Foundation and American Heart Association
ACS: acute coronary syndromes
AMI: acute myocardial infarction
AUC: area under the curve
BMS: bare metal stent
Cmax: maximum concentration
DES: drug-eluting stent
ESC: European Society of Cardiology
GP IIb/IIIa: glycoprotein IIb/IIIa
IV: intravenously
LTA: light transmission aggregometry
MEA: multiple electrode aggregometry
NSTEMI: non-ST-segment elevation myocardial infarction
PCI: percutaneous coronary intervention
PD: pharmacodynamics
PK: pharmacokinetics
PRI: platelet reactivity index
PRU: P2Y12 reaction units
STEMI: ST-segment elevation myocardial infarction.
